#### Pulmonary air leak in the newborn

This condition is characterized by air leak from the lung identified by X-ray imaging, including pneumothorax, pneumomediastinum, pulmonary interstitial emphysema, and pneumopericardium.

#### Adverse events

Serious adverse events (SAEs) include death, prolonged hospitalization, and persistent disability, which are expected to be closely related to surfactant administration in the opinion of local medical investigators. SAEs will be reported within 24 h to the local Ethics Committee and Data and Safety Monitoring Committee (DSMC), and will be reported within 3 working days to coordinating centers. Any recommendations will be disseminated to local investigators. Adverse events are characterized by operation failure as described above or any clinical deterioration, including BPD, proven or advanced NEC, IVH (grades III and IV), severe ROP, massive pulmonary hemorrhage and pulmonary air leak, which are related to surfactant administration. AEs will be reported to the coordinating centers every month and will be closely monitored by the DSMC.

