### Blinding

Operators and care providers will not be blinded, and the outcome assessors and data analysts will be blinded to the intervention. Decisions regarding ongoing treatments will be made according to every unit’s guidelines and clinical practice. The authors had two meetings before the study to obtain consensus for neonatal care.

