#### NEC (proven and advanced)

Proven NEC (stage II) encompasses the signs of stage I plus the absence of bowel sounds with or without abdominal tenderness. Abdominal tenderness is present, and some infants have cellulitis of the abdominal wall or a mass in the right lower quadrant. Infants with stage IIA are mildly ill, whereas those with stage IIB NEC are moderately ill and have mild metabolic acidosis and thrombocytopenia. Findings on abdominal imaging include intestinal dilation, ileus, ascites, and pneumatosis intestinalis, which is the defining feature of stage II.

Advanced NEC (stage III) is the most severe form. In stage IIIA, the bowel is intact, whereas stage IIIB is characterized by bowel perforation visualized as a pneumoperitoneum on the abdominal radiograph. Infants with advanced NEC are critically ill. In addition to the signs shown in the less severe stages, they typically have hypotension, bradycardia, severe apnea, and signs of peritonitis (abdominal distention and marked tenderness). Laboratory signs include a combined respiratory and metabolic acidosis, neutropenia, and disseminated intravascular coagulation [11].

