## Discussion

In recent years, the LISA method has been accepted by increasing number of doctors. However, the potential benefit of LISA is still not clear. Moreover, an increased incidence of spontaneous intestinal perforation in extremely premature infants has been reported [15]. A meta-analysis showed that LISA showed effects on reducing the rate of MV during the first 72 h and the combination of BPD mortality and morbidity based on previous trials, which compared the effects of LISA with conventional surfactant technique (including intubation and ventilation by bagging or ventilator). We found that previous studies focused more on the procedure of performing LISA but less on the clarity of the potential mechanism [16, 17]. In fact, pulmonary compliance will change during the period of surfactant administration, and the peak pressure of ventilation barely changed spontaneously, even with use of a more advanced ventilator. A preliminary idea is that the whole procedure of surfactant administration without ventilation may contribute most to the advantages of LISA [18]. Thus, if correct, we would have further comprehension of LISA, and further knowledge would encourage more efforts on applying optimal peak pressure to surfactant delivery instead of trying to require all doctors to learn the method of LISA in China.

The delivery of surfactant as soon as possible has been known to help the distribution of the surfactant [19] In a previous study, the LISA procedure may took 0.5–5 min (average 2-3 min), which is longer than that of conventional method. Desaturation and apnea are the main complications of LISA [20, 21]. This situation is seldom seen in conventional surfactant administration. The contradiction of “time and effects” between LISA and conventional method may suggest some potential benefits of LISA. In this trial, the time required to perform the procedure would also be evaluated, because of the variable data of previous studies.We hope it will give us more information of the reason and a relatively standard operation of LISA can be set.

To our knowledge, this trial will be the first multicenter randomized controlled trial to evaluate the potential benefits of LISA and will give a more objective evaluation of LISA.

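### The SAE and AE definitions contain a local causality judgment, so expedited safety reporting can be incomplete and can differ by arm; intestinal perforation, a concern the protocol itself cites, is on no list

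*Protocol article*

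**What the plan says.** The protocol article, under Adverse events, names three kinds of serious event and then qualifies them as events "which are expected to be closely related to surfactant administration in the opinion of local medical investigators". The reporting duty attaches to that definition: "SAEs will be reported within 24 h to the local Ethics Committee and Data and Safety Monitoring Committee (DSMC"), with three working days allowed for the coordinating centers.

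Non-serious adverse events are described as "operation failure as described above or any clinical deterioration, including BPD, proven or advanced NEC, IVH (grades III and IV), severe ROP", and the list closes with "massive pulmonary hemorrhage and pulmonary air leak, which are related to surfactant administration". These go to the coordinating centers monthly and are watched by the monitoring committee.

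On who knows the arm, the Blinding section says "Operators and care providers will not be blinded, and the outcome assessors and data analysts will be blinded to the intervention". Under Data collection, the participating doctor in each unit enters the data.

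On perforation, the Discussion notes after introducing LISA that "an increased incidence of spontaneous intestinal perforation in extremely premature infants has been reported". The only other mention of bowel perforation is in the NEC definition, where "stage IIIB is characterized by bowel perforation visualized as a pneumoperitoneum on the abdominal radiograph".

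**The concern.** Seriousness and causality are separate judgments, and the definition merges them. Followed as written, a death that the local investigator does not think closely related to the procedure is not an SAE, so the 24-hour report is not triggered.

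This matters because the events concerned are common complications of prematurity. A clinician can seldom attribute one case of IVH, NEC or BPD to one procedure. An effect of technique would show as a difference in rates between arms, and that requires counts not already screened for attribution. If the person screening knows the arm, the screening can also differ between arms. What is at stake is how quickly and how evenly the monitoring committee learns of serious events.

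Perforation is a related but separate gap. The protocol cites it as a concern in extremely premature infants and enrols from 25 weeks, but its lists give it no entry that is free of the relatedness condition.

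**Working it through.** No figure in the documents is at stake, so the main check sets the sections side by side.

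**Step 1. Which events depend on the filter?**

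| Event | Under Adverse events | Collected elsewhere without a relatedness condition? |
|---|---|---|
| Death | SAE if judged closely related | Yes, primary outcome |
| Longer hospital stay | SAE if judged closely related | Yes, duration of hospitalization is a secondary outcome |
| BPD | AE if related | Yes, primary outcome |
| Pneumothorax, massive pulmonary hemorrhage | AE if related | Yes, secondary outcomes (within 48 h of surfactant) |
| Procedure failure | AE if related | Yes, secondary outcome |
| NEC, severe IVH, ROP | AE if related | Yes, under Other data |
| Spontaneous intestinal perforation | Not named; could enter as a clinical deterioration if related | No listed item |

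Mechanical ventilation and hsPDA are also outcomes with no attribution condition. For every row except the last, the filter changes how and when an event is reported, not whether it reaches the final comparison.

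**Step 2. Can the reported streams differ by arm?** Let p1 and p2 be the true event rates in the two arms, and q1 and q2 the shares of events that local investigators judge related. With equal arm sizes:

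reported ratio = (p1 × q1) / (p2 × q2)

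If the true rates are equal, this reduces to q1/q2. Any difference in attribution then appears as a difference in harm. If the rates differ, unequal attribution can hide it. The documents give no values for q1 or q2. Blinding tells us only that care providers know the arm, and Adverse events describes no blinded or central review. That the judging investigator is unblinded is inferred from Blinding and Data collection; the Adverse events section does not say so.

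**Step 3. Illustration for perforation.** The documents give no rates, so those below are assumptions, as is the share q of cases that pass the filter (equal in both arms). The 300 per arm is the recruitment target under Sample size calculation; the test is two-sided at 0.05.

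power = Φ{ [ |p2 − p1| − 1.96 × √(2p̄(1 − p̄)/n) ] / √[ p1(1 − p1)/n + p2(1 − p2)/n ] }, where p1 and p2 are each multiplied by q and p̄ is their mean.

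For 2% vs 5%:
- q = 1 (6 vs 15 expected cases): (0.03 − 1.96 × 0.01501)/0.01496 = 0.039, power 0.516
- q = 0.5 (1% vs 2.5%): (0.015 − 1.96 × 0.01071)/0.01069 = −0.560, power 0.288
- q = 0.25 (0.5% vs 1.25%): (0.0075 − 1.96 × 0.00760)/0.00760 = −0.97, power 0.165

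| Assumed true rates | q = 1 | q = 0.5 | q = 0.25 |
|---|---|---|---|
| 1% vs 3% | 0.416 | 0.233 | 0.137 |
| 2% vs 5% | 0.516 | 0.288 | 0.165 |
| 3% vs 8% | 0.767 | 0.465 | 0.259 |

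The filter weakens detection of an event that has no other route. Even complete recording leaves power below 0.8 in each of these scenarios.

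**The case against.** The strongest reply is that the safety comparison does not rest on SAE forms. Mortality and the main morbidities are outcomes or collected data with no attribution condition, and outcome assessors and analysts are blinded. The Data monitoring committee section also gives the committee interim data analysis. This stands. A reader might infer that the trial could miss an excess of deaths; the documents do not support that.

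The qualifying clause could also be read as a description of SAEs rather than a limit on them. Its reference to the local investigators' opinion points to a case-by-case judgment, so the limiting reading is the natural one. If the sponsor meant otherwise, the wording still needs correcting.

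Other stronger readings also fail:

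- **Wrong exposure.** Both arms receive surfactant, so a reader might think the filter asks about the drug rather than the randomised technique. In this article, however, surfactant administration usually means the procedure: the Abstract compares two methods of it, the names of both arms contain it, and the AE list includes operation failure.
- **Misfiling.** A reader might expect spontaneous perforation to be recorded as NEC stage IIIB. The NEC definition requires the signs of the milder stages as well, so perforation without NEC does not meet it. Misfiling is conjecture.
- **The only LISA harm raised.** The Discussion also names desaturation and apnea as the main LISA complications. These are addressed through the saturation and heart rate recordings and the failure criteria in both arms.
- **Perforation not collected.** The full protocol and case report form are not at hand and may include it. What can be said is that the article's lists name other morbidities and not this one.

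**Conclusion.** The point holds in a limited form. The causality condition is stated text in the SAE and AE definitions, not a detail lost in condensing the protocol. Followed as written, it can leave the expedited SAE reports and the monthly AE reports incomplete, and incomplete to different degrees by arm. The consequence is confined to SAE status, expedited reporting and timely oversight.

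Its size cannot be derived from the documents, which give no mortality or perforation rate and no share of events judged related. The conclusion assumes that local investigators know the arm and that the two committee names in the article (DSMC and DMC) refer to the same body.

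The perforation gap is a lesser, supporting point. The concern is cited, infants from 25 weeks are enrolled, and no listed item names the event. An added item would give a complete count, but the power figures are illustrations on assumed rates and give no ground for claiming that the trial could settle the question. Overall this is a cheap improvement worth making, not a threat to the primary comparison.

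**What to change.** - Define SAEs by seriousness alone, and remove the relatedness condition from the AE definition.
- Report every death and every other SAE after randomisation to the monitoring committee within 24 hours.
- Record relatedness to the technique as a separate field, preferably assessed by someone blinded to the arm.
- Tabulate all events by arm, whatever the attribution.
- Add spontaneous intestinal perforation, distinct from NEC stage IIIB, as a case report form item if the form does not already have it. Report it descriptively by arm, without claiming that the trial is powered for it.

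The cost is revised wording in one section, the relatedness field, at most one further form item, and more SAE forms from the 14 units. Sample size and primary analysis are unchanged.

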### Data collection

All data will be collected from patient records. Data will be entered by the doctor who participated in the study of the individual NICU on a web-based electronic case record form and a written case report form. Access to the form will be protected by password, and infants may be identified by number only. A full-time coordinator will be responsible for monitoring the progress of the study and collecting feedback information from each unit. Data will be collected at the following schedule (Table 1).

**Table 1 Tab1:** Timeline of the study and clinical data collection

TIMEPOINT	Study Period				
	Enrollment	Allocation	Post-allocation		
	Birth to 0	0	Surfactant administration (-10min-+10min)	72 hours after birth	At 36 weeks PMA or at discharge
**Enrolment:**					
**Eligibility screen**	X				
**Informed consent**	X				
**Allocation**		X			
**Intervention**					
LISA			X	X	X
LPPSA			X	X	X
**Assessments**					
**Primary outcomes** 1.Need for ventilation during the first 72 hours				X	
2. Mortality 3. BPD					X
**Secondary outcomes** Need for and the duration of MV (days), duration (days) of non-invasive respiratory support, severe co-morbidities, pneumothorax, massive pulmonary hemorrhage within 48 h of surfactant administration, hemodynamically significant patent ductus arteriosus that needs medical or surgical intervention, Duration of hospitalization, Failure rate of LISA or LPPSA			X	X	X

*LPPSA* surfactant administration followed by low peak pressure, *LISA* less invasive surfactant administration

### Data monitoring committee

An independent Data Monitoring Committee (DMC) belonging to the Central Ethics Committee of Women’s Hospital School of Medicine, Zhejiang University, has been established for the trial. This committee will perform interim data analysis, investigate compliance with the trial, and monitor adverse events.

### Statistical methods

All data will be analyzed using SPSS version 20.0. To compare primary and secondary outcomes between the two groups, Student’s t-test (continuous variables) and the chi-squared test (categorical variables) will be used. The two-level hierarchical linear regression model or the logistic regression model, whichever is appropriate, will be applied for the comparison of the outcomes between the two groups, accounting for the infants’ characteristics, such as gestational age, birthweight, sex, appropriateness for gestational age, delivery mode, and pregnancy complications, and center variables, such as number of beds in the NICU and the number of infants with gestational age < 32 weeks. *P* < 0.05 will be regarded as statistically significant.

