**Methods:**

The **L**ISA **O**r **L**ow **P**eak **P**ressure trial is to be conducted in 14 tertiary neonatal intensive care units in China. A total of 600 preterm infants born with gestational age between 25^0/7^ and 31^6/7^ weeks and with a primary diagnosis of RDS will be involved in the study. Infants will be randomized to the LISA or LPPSA group when surfactant therapy is indicated. Primary outcomes include mortality, severity of bronchopulmonary dysplasia at 36 weeks of postmenstrual age (PMA), and mechanical ventilation (MV) in the first 72 h of life. Secondary outcomes include the days of MV, duration of all sorts of non-invasive respiratory support, fraction of inspired oxygen, oxygen saturation before and after surfactant administration, and time required to perform the procedure for surfactant administration. The incidence of comorbidities, including retinopathy of prematurity (ROP), necrotizing enterocolitis (NEC), intraventricular hemorrhage (IVH), hemodynamically significant patent ductus arteriosus (hsPDA), pneumothorax, and massive pulmonary hemorrhage within 48 h of surfactant administration, and the failure rates of each technique will be determined.

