### Sample size calculation

The proposed sample size is calculated according to the incidence of BPD. According to previous reports and the average data from every unit involved in the trials [6, 7], approximately 60% of infants born at 25^+ 1^ to 27^+ 6^ gestational weeks and approximately 15% among those born at 28^+ 1^–31^+ 6^ gestational weeks have developed BPD during the past 5 years. The presumed incidence of BPD will be approximately 25% in the pooled population of our trial. Considering an alpha error rate of 0.05 and a power of 0.8 to detect an expected 20% reduction in the incidence of BPD, 258 infants will be enrolled in each group. To consider factors such as data incompleteness, failure to follow up, or early dropout, we plan to recruit 300 preterm neonates for each group.

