#### Secondary outcomes

The secondary outcomes will be as follows:
Need for and duration of MV (days) during of hospitalizationDuration of noninvasive respiratory support (days)Duration of oxygen need.Heart rate and oxygen saturation before and after surfactant administration in every 30 s for 10 min.Incidence of pneumothorax and massive pulmonary hemorrhage within 48 h of surfactant administrationSevere neonatal diseases including and hemodynamically significant patent ductus arteriosus (hsPDA) that needs medical or surgical interventionDuration of hospitalizationFailure rate of operation (including LISA or LPPSA technique)Time required to perform the procedure of surfactant administration.

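### The planned comparison of heart rate and oxygen saturation around surfactant administration does not name the infant's own pre-procedure value as a covariate, so precision on a secondary outcome may be lost

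*Protocol article*

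**What the plan says.** The Protocol article, under Secondary outcomes, lists "Heart rate and oxygen saturation before and after surfactant administration in every 30 s for 10 min". Table 1 under Data collection has a column headed "Surfactant administration (-10min-+10min", which fits readings taken on both sides of the procedure. The Methods part of the abstract words the outcome differently, as "fraction of inspired oxygen, oxygen saturation before and after surfactant administration". FiO2 does not appear in the Secondary outcomes list of the main text.

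Statistical methods gives one rule for all primary and secondary outcomes. For the simple comparison, "Student’s t-test (continuous variables) and the chi-squared test (categorical variables) will be used". Then "The two-level hierarchical linear regression model or the logistic regression model, whichever is appropriate, will be applied for the comparison of the outcomes", "accounting for the infants’ characteristics, such as gestational age, birthweight, sex, appropriateness for gestational age, delivery mode, and pregnancy complications", and two centre variables (NICU beds and the number of infants below 32 weeks). That makes six infant covariates and two centre covariates. None is the infant's heart rate or saturation before the procedure. The section does not say whether the t-test is applied to the post-surfactant value, to the change, or to some summary of the series.

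**The concern.** When the same quantity is measured in the same infant shortly before and shortly after the intervention, the earlier value is usually a strong candidate predictor of the later one. It is likely to be more informative about saturation ten minutes later than the size of the unit. A two-sample t-test cannot use it as a covariate. Applied to the post value, the test ignores the baseline. Applied to the change, it forces the slope on baseline to be 1, which is inefficient unless the correlation is close to 1.

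What is at stake is the width of the confidence interval for the effect of technique on the immediate physiological response. That response matters to this trial: the Discussion names desaturation and apnea as the main complications of LISA, and the trial is framed around mechanism. A chance difference between the arms in starting values would also stay in a post-value estimate, although the standard error already allows for it.

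**Working it through.** **The plan's own figure.** There is none for these outcomes. The only power statement is for BPD: "Considering an alpha error rate of 0.05 and a power of 0.8 to detect an expected 20% reduction in the incidence of BPD". No effect size, standard deviation, correlation or power is given for heart rate or saturation, so the starting power and the correlation below are assumptions.

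**Inputs**
- Alpha 0.05 (Sample size calculation; sidedness is not stated, two-sided assumed), so z = 1.96.
- Starting power of the t-test 80% (assumed), so z = 0.8416. The sum is 2.8016.
- Correlation rho between the pre- and post-procedure values: assumed, shown from 0.3 to 0.7, equal variances before and after.
- 300 infants per group (Sample size calculation).

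**Variances, in units of the post-value variance**
- t-test on the post value: 1
- t-test on the change: 2(1 − rho)
- linear model with the baseline as covariate: 1 − rho²

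The adjusted model has variance 1 − rho² relative to the post-value test, and (1 − rho²)/[2(1 − rho)] = (1 + rho)/2 relative to the change-score test.

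**Power after adjustment**
- from 80% on the post value: Φ(2.8016/√(1 − rho²) − 1.96)
- from 80% on the change: Φ(2.8016/√((1 + rho)/2) − 1.96)

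Example at rho = 0.5: both ratios equal 0.75 and √0.75 = 0.866. Then 2.8016/0.866 − 1.96 = 1.275, and Φ(1.275) = 0.899.

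| rho | from 80%, post-value t-test | from 80%, change-score t-test |
|---|---|---|
| 0.3 | 83.6% | 93.5% |
| 0.4 | 86.4% | 91.7% |
| 0.5 | 89.9% | 89.9% |
| 0.6 | 93.8% | 88.0% |
| 0.7 | 97.5% | 86.0% |

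Each column takes its own t-test as having 80% power, so the two columns refer to different true effects except at rho = 0.5.

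**Dependence on the starting power.** At rho = 0.5 the gain is 11.9 points from a start of 50%, 11.8 from 70%, 9.9 from 80%, 6.3 from 90% and 3.6 from 95%.

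**In terms of effect size.** With 300 per group, 80% power for the post-value test corresponds to a difference of 2.8016 × √(2/300) = 0.23 SD. At rho = 0.5:
- 0.2 SD: 68.8% rises to 80.7%
- 0.3 SD: 95.7% rises to 98.9%
- 0.4 SD: 99.8% rises to practically 100%

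**The case against.** The strongest case against runs as follows.

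- **The list is open.** The covariates are given as examples, so a reader who infers that the plan rules out the baseline value goes further than the text. This stands: the value is not named, which is different from being excluded. But an open list is no commitment, and the t-test has no place for a covariate.
- **This is detail for an analysis plan.** One paragraph covers every outcome, and the full plan is not shown. This stands in part. However, the article does choose a test for continuous secondary outcomes and names eight covariates, down to bed count. The point concerns that choice, for which a better method exists using planned readings.
- **The analysed quantity is unknown.** If the t-test is on the change, starting imbalance does not carry over in full, and at rho = 0.7 the gain is about 6 points, not 17.5. This stands, which is why both readings are shown.
- **The correlation may be low.** Infants enter only if stabilised on PEEP 6–8 cmH2O and needing FiO2 of at least 0.3, which may narrow the baseline spread, and later values also reflect apnea or desaturation during the procedure. At rho = 0.3 the gain over a post-value test is under 4 points. This stands.
- **The comparator is the weaker analysis.** The planned regression on gestational age, birthweight and the rest may already recover some precision. This stands, and the documents do not allow the share to be estimated.

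**Conclusion.** The point holds as a modest improvement. Pre-procedure heart rate and saturation are to be recorded, and the stated comparison does not commit to using them as a covariate. On the assumption of 80% starting power, adjustment brings power to about 84%, 90% and 98% at rho 0.3, 0.5 and 0.7 against a post-value t-test. Against a change-score t-test it brings power to about 90% at 0.5 and 86% at 0.7. Neither rho nor the 80% is in the protocol for these outcomes, so a gain of 10 points should be read as an illustration and not as a finding about this trial. For differences of 0.3 SD or more, with 300 per group and rho 0.5, the gain over a post-value test is about 3 points or less.

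Two stronger readings are not supported. A reader might infer that the unadjusted comparison is biased; under randomisation it is not, since chance imbalance is covered by the standard error. A reader might also infer damage to the main result; the primary outcomes and the sample size are not affected. FiO2 is on weaker ground than the other two measures, because only the abstract lists it as an outcome.

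**What to change.** Add one sentence to Statistical methods. For heart rate and oxygen saturation, the main comparison is a linear model, within the two-level model already planned, of the post-surfactant value on arm, the same infant's pre-procedure value and the covariates already listed; the t-test is not the main analysis for these outcomes. Two definitions are needed to make it workable:

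- **Post-surfactant value:** for example, the mean of the readings over the 10 min after surfactant. The protocol records a series and defines no single value.
- **Baseline:** the mean of the readings before laryngoscope insertion. Both arms use laryngoscopy, and readings taken after it but before surfactant may already reflect the assigned technique.

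Do the same for FiO2 only if it is kept as an outcome, and bring the abstract and the Secondary outcomes list into line on that.

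The cost is wording, settled before any comparison by arm. The readings are already planned, SPSS fits the model, and no infants, visits or changes in care are needed. Marking the time of laryngoscope insertion against the readings is the one item to confirm on the case report form.
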